### Interventions

Group A receives the standard invitation letter for a NHS Health Check, sent from the central unit that organizes Health Check invitations. This comprises a single-page letter from the individuals’ GPs, inviting them to make an appointment at their general practice to receive the Check or to visit a local participating pharmacy, plus an information sheet. Individuals are sent a reminder letter if they do not attend for a Health Check within 12 weeks of their first invitation.

Group B: Participants are sent the QBE questionnaire, with prepaid return envelope and covering letter 7 days before they are sent the standard NHS Health Check invitation letter and information sheet (plus reminder letter at 12 weeks, where appropriate). The QBE questionnaire is a two-page, eight-item questionnaire with one example question at the beginning. Six questions are derived from Theory of Planned Behavior [25] concepts, and two questions are based on the notion of anticipated regret. All questions are on a 7-point scale and have high readability. The questionnaire was subjected to feasibility and acceptability testing, with five individuals involved in the delivery of the NHS Health Checks program and 15 individuals from the local population in the target age range for a Health Check. Based on this feedback, the questionnaire was further refined before being used in the trial.

Group C: Participants are sent the QBE questionnaire, with prepaid return envelope and covering letter 7 days before they are sent the standard NHS Health Check invitation letter and information sheet (plus reminder letter at 12 weeks, where appropriate). The covering letter differs from that received by Group B, as participants are offered a £5 retail voucher as an incentive to return the questionnaire.

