### Sample size

It will be important to detect even modest increments in screening uptake between trial arms, because in a public health program, small effects may yield substantial benefits across the population at risk. We make the statistically conservative assumption that the underlying proportion of people invited who actually receive a Health Check is about 50%. With 4,263 participants in each trial arm, with 12,789 in total, this provides more than 90% power to detect a difference in uptake of Health Checks between each active treatment arm and the standard intervention arm of at least 4%. These calculations are based on 5% significance level by using a Bonferroni correction for three comparisons. The calculations were performed in Stata version 12 [26]. Because present rates of Health Check uptake are below 50% in the study area, slightly greater power may be realized in the study. No planned interim analysis and no stopping guidelines exist, as this trial has a low risk of adverse events.

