### Secondary analyses

To understand the processes of responding to the intervention, analyses will be implemented to determine whether completing the QBE questionnaire, as opposed to receiving but not completing the questionnaire, is necessary to obtain the observed effects. We will compare the proportions of patients who attend Health Checks among participants who received and completed the questionnaire for the QBE arm (completers) and the QBE + incentive arm (incentive-completers), as well as participants in the QBE arm who received but did not complete the questionnaire (noncompleters) and participants in the QBE + incentive arm who received but did not complete the questionnaire (incentive-noncompleters), and those who did not receive the questionnaire.

We will also examine whether having higher or more-positive cognitions (that is, attitude, subjective norms, perceived behavioral control, anticipated regret, intentions) about the Health Check, when completing the QBE questionnaire is associated with increased rates of attendance. Therefore, we will compare the proportions of patients who attend Health Checks for positive completers (those with high scores on the cognitions) and negative completers (those with low scores on the cognitions). If significant differences in uptake appear between the QBE and QBE + incentive arms, we will examine whether these are mediated by differences in cognitions [30].

The response rate to the QBE questionnaire will be analyzed both overall, for each treatment group, and by deprivation quintile. The distributions of responses to questionnaire items will be evaluated by deprivation quintile. We plan to access the results of the participants’ Health Checks, in terms of level of cardiovascular risk, and compare these by trial arm. We will compare Health Check results for questionnaire responders and nonresponders. These analyses will thus describe the pattern of response to the intervention in terms of both deprivation category and level of cardiovascular risk.

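### The only stated test of whether cognition scores predict attendance splits 7-point scores into high and low, which loses information and makes the answer depend on the cut

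*Protocol article*

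**What the plan says.** The Interventions section describes an eight-item questionnaire, with six items from the Theory of Planned Behavior and two on anticipated regret. On scoring it states: "All questions are on a 7-point scale".

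The Secondary analyses section poses a graded question: "We will also examine whether having higher or more-positive cognitions" go with increased attendance. It then names one analysis to answer it: "we will compare the proportions of patients who attend Health Checks for positive completers (those with high scores on the cognitions"). The group on the other side of this contrast is described as "negative completers (those with low scores on the cognitions"). No analysis of attendance against the full score is stated. The article does not say where high and low divide, whether middle scores are kept, or whether items are combined.

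Cognition scores have one other stated use. If uptake differs significantly between the two questionnaire arms, "we will examine whether these are mediated by differences in cognitions". The article does not say in what form the scores enter that step.

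**The concern.** The question is about degree, but the planned answer has two levels. A high/low split treats everyone within a group as alike and treats people just either side of the cut as different in kind. Two things follow. The association is estimated less precisely than the collected data allow, and the result can change with the choice of cut.

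The analysis bears on the trial's reasoning. The Background argues that the question-behaviour effect is stronger in people with favourable attitudes and intentions, that it could therefore widen inequalities, and that an incentive may bring in returners with less favourable attitudes. Only people in Groups B and C who return the form contribute scores, so the sample is already reduced before any split is made.

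The absence of a cut-point is not the complaint, since that can be left to the analysis plan. The point is the choice of a two-group comparison, which the article does state.

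**Working it through.** **1. The plan's own figure.** The article gives no sample size or power for the cognition analysis. Its nearest figure is the primary sample size: "With 4,263 participants in each trial arm, with 12,789 in total". For 50% v 54%, two-sided α = 0.05/3 (sidedness assumed) and 90% power, the two-proportion formula gives 4,213 per arm. With continuity correction:

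n = (4,213/4) × [1 + √(1 + 4/(4,213 × 0.04))]² = 4,263

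This matches the plan; 3 × 4,263 = 12,789, and power at 4,263 is 0.904. The figure is sound and this point does not touch it.

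**2. Information kept by a split.** For a linear association, the efficiency of a split relative to the full score is the squared correlation between the score and its high/low indicator. For a normal score cut at quantile q, with c the cut:

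efficiency = φ(c)² / [q(1 − q)]

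At the median this is 0.3989² / 0.25 = 2/π = 0.637.

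| Cut of a normal score | Efficiency | Loss |
|---|---|---|
| 50/50 | 0.637 | 36% |
| 30/70 | 0.576 | 42% |
| 25/75 | 0.539 | 46% |
| 20/80 | 0.490 | 51% |
| 10/90 | 0.342 | 66% |

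**3. The same for a 7-point score.** The distributions are assumptions, because the article reports none. Worked case: uniform on 1 to 7 has mean 4 and variance 4. With high = 5 or more, p = 3/7 and the covariance is 18/7 − 4 × 3/7 = 6/7. The efficiency is (6/7)² / [4 × (3/7)(4/7)] = 0.75.

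| Assumed distribution | Cut | Efficiency | Loss |
|---|---|---|---|
| Uniform | nearest the middle | 0.750 | 25% |
| Bell-shaped (mean 4, SD 1.5) | nearest the middle | 0.656 | 34% |
| Skewed to the top (3, 3, 5, 9, 15, 25, 40%) | best cut | 0.711 | 29% |
| Same | top category only | 0.492 | 51% |
| More skewed (2, 1, 2, 5, 10, 20, 60%) | best cut | 0.712 | 29% |
| Same | top category only | 0.565 | 43.5% |

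Every cut tried loses at least a quarter.

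**4. Power.** Inputs:
- Return rate: assumed. 20% of 2 × 4,263 = 8,526 is about 1,700; 10% is about 850.
- Attendance: 50%, from the Sample size section's assumption that "the underlying proportion of people invited who actually receive a Health Check is about 50" per cent. Applying it to returners is a further assumption.
- Slope β, the log odds ratio per SD: assumed and varied.
- Test: two-sided 5%, one score at a time, median split of a normal score.

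z = √(n × 0.25 × β² × efficiency), and power = Φ(z − 1.96).

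Worked case, n = 1,700 and β = 0.14: 1,700 × 0.25 × 0.0196 = 8.33, so z = 2.89 and power is 82%. With the split, 8.33 × 0.637 = 5.31, so z = 2.30 and power is 63%.

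| n | β | Full score | Median split |
|---|---|---|---|
| 1,700 | 0.14 | 82% | 63% |
| 1,700 | 0.20 | 98% | 91% |
| 1,700 | 0.30 | >99% | >99% |
| 850 | 0.14 | 53% | 37% |
| 850 | 0.20 | 83% | 64% |
| 850 | 0.30 | 99% | 94% |

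**5. Precision.** At efficiency 0.637 the standard error of the per-SD slope is 1/√0.637 = 1.25 times as large. At 1,705 returners (20% of 8,526), the slope detectable with 80% power is (1.96 + 0.84) × √(0.25/1,705) = 3.4 percentage points per SD with the full score. With the split it is 3.4 × 1.25 = 4.3.

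**The case against.** The strongest reply has four parts.

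- **The loss cannot be read off the document.** A single figure of about a third needs a median split, a roughly normal score and a linear association, and the article states none of these. This stands, so the loss is given as a range under named assumptions. A threshold-like relation, or a comparison of extreme groups with the middle dropped, would give other figures.
- **The power cost may be small.** It is marked only for weak associations. At 0.30 per SD with 1,700 returners, the answer to whether cognitions predict attendance would hardly change. This stands.
- **The contrast has a rationale.** It follows the Background's argument about favourable attitudes, and comparing proportions suits the trial's preference for absolute differences. That justifies showing the table. It does not justify making it the only stated test, because a risk difference per scale point is also absolute.
- **A condensed article leaves detail to the analysis plan.** This is true of the cut, the scoring and any supporting model, and the article does not rule out a model of the full score. It does, however, state the two-group comparison as its method, and that can be judged as written.

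A reader might also infer that answers crowd at the top of the scale, or that the split damages the mediation analysis. The documents support neither. The Interventions section gives only the scale length, so the skewed distributions in the working are illustrations. The mediation step is conditional on a difference between the questionnaire arms and is not said to use the high/low groups.

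**Conclusion.** The point holds as a minor improvement. The article asks a graded question of graded scores and states only a high/low comparison to answer it. Under a roughly linear association, the information lost is 36% at a median split of a normal score and about 25% to 50% or more across the cuts and distributions tried. The loss in power at a median split with 1,700 returners ranges from about 19 percentage points at a log odds ratio of 0.14 per SD to almost nothing at 0.30. Return rate, slope, score distribution and cut are all assumptions.

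It would be wrong to infer that the trial's main findings are at risk. The comparison is secondary, explanatory and non-randomised, and is confined to people who returned the form. The primary outcome, the sample size and the between-arm comparisons are unaffected.

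**What to change.** Make the stated analysis a model of attendance on each cognition score, taken as continuous or ordinal. Report a risk difference per scale point or per SD, with a term for curvature so that a threshold or plateau can show. Adjust for age, gender, month of invitation and deprivation quintile, which the trial already uses elsewhere, and allow for practice. Keep the attendance proportions for high and low scorers as a descriptive table, with the cut fixed before the data are examined.

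The cost is a change of wording, slightly more analysis work and a less simple display. No new data are needed, since the questionnaire already collects the scores, and with recruitment reported as ongoing the change can be made before analysis.

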### Financial incentives to increase response rates to questionnaires

Strong evidence suggests that financial incentives for questionnaire return increase response rates. A systematic review, including 94 trials with a pooled total of 160,004 participants, found that the odds of returning a postal questionnaire were almost doubled if a financial incentive was offered [20]. As the Question-Behaviour Effect is greater among individuals who return a questionnaire [17], incentivizing questionnaire return may increase the size of any effect of a questionnaire on uptake of the NHS Health Check. A meta-analysis of 85,671 participants in 88 randomized trials of financial incentives to increase response rates for mailed questionnaires reported a significant increase in response rates for incentives up to the value of $5 [21].

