### What is the potential impact on socioeconomic inequalities in uptake?

Death rates from coronary heart disease are highest in areas of greatest deprivation [1], so considering socioeconomic inequalities in the evaluation of any intervention to increase uptake of NHS Health Checks is important. Although evidence suggests that enhanced invitation methods, such as a QBE-based questionnaire, increase uptake of screening and performance of health-related behaviors, we do not know their impact on the NHS Health Checks, a relatively new program. The impact of the QBE on inequalities in uptake is also unknown. Individuals experiencing greater levels of deprivation may find it more difficult to convert their positive attitudes toward Health Checks, and their intentions to attend, into action. One of the possible mechanisms of action of the QBE is that it makes individuals’ attitudes more cognitively accessible and thus may increase the likelihood that individuals from deprived backgrounds attend. Alternatively, although we do not know if level of deprivation influences attitudes toward NHS Health Checks, evidence from cancer screening suggests that individuals experiencing greater levels of deprivation perceive fewer benefits and greater barriers to attending [22].

The QBE is stronger for individuals with positive attitudes toward, and intentions for, the behavior [17]; therefore the QBE may enhance inequalities in uptake, if any do exist. The offer of a financial incentive may increase questionnaire return rates only among those with already positive attitudes toward NHS Health Checks, so should result in increased uptake. However, if the offer of a financial incentive increases questionnaire return rates among those with less-positive attitudes, it is likely to have a lesser impact on uptake.

Little research examines how and if incentives influence uptake of screening differentially across deprivation [23]. The offer of a financial incentive may be most attractive for individuals who are experiencing deprivation and so may increase the strength of the QBE on Health Check uptake, particularly in individuals from deprived backgrounds. It will be important to consider inequalities in uptake in any investigation of the impact of the QBE on uptake of NHS Health Checks.

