**Trial flow diagram.**

### Setting and participants

The trial is being implemented in two London Boroughs, which are ranked 14th and 16th most-deprived local authorities in England [24]. Both boroughs are typical of areas that are in need of intervention to increase the number of individuals attending for their NHS Health Check, as uptake is below the national average (49%) [7]. In 2013/2014, 32% of individuals invited for a Health Check attended in one borough, and 38%, in the other [7].

All general practices in these boroughs are eligible and asked to consent to their patients participating in the trial. Patients are included in the trial only if their practice has provided consent. Consent to use questionnaire data is presumed, based on participants returning a questionnaire. All participants in the consented practices who are eligible to receive an NHS Health Check are included in the trial, with no exceptions from randomization or analysis.

Individuals are eligible for an NHS Health Check if they are aged between 40 and 74 years and have no existing CVD-related comorbidities and are not already prescribed antihypertensive drugs or statins. Individuals are invited for a Health Check through a cross-borough call and recall system, organized at a central unit that serves both boroughs. Each month, eligible patients are identified centrally and a pre-notification list of patients is sent to each practice for them to perform a second check for eligibility/suitability. After this, the list is considered to be ”clean”, and these patients are invited for an NHS Health Check in that month by standard invitation letter. The individual clean lists for each participating practice is the sampling frame for this trial.

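### Whether cognitions mediate the voucher effect is examined only if B versus C is significant; it should be examined, as exploratory, whatever the P value

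*Protocol article*

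**What the plan says.** The protocol article, Secondary analyses, makes one explanatory analysis depend on a test result: "If significant differences in uptake appear between the QBE and QBE + incentive arms, we will examine whether these are mediated". The mediators it has in mind are the cognition scores from the questionnaire. It does not say whether significance here means the multiplicity-adjusted or the unadjusted level. Statistical methods includes B versus C among the comparisons to be adjusted.

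The other process analyses carry no such condition. Uptake is compared among completers and noncompleters of each questionnaire arm, and between completers with high and low cognition scores. For return, "The response rate to the QBE questionnaire will be analyzed both overall, for each treatment group, and by deprivation quintile".

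The Background gives two reasons to care about this contrast. On returns, it reports that "the odds of returning a postal questionnaire were almost doubled if a financial incentive was offered". On who returns, the section on socioeconomic inequalities says that "if the offer of a financial incentive increases questionnaire return rates among those with less-positive attitudes, it is likely to have a lesser impact". The impact meant there is the one on attendance.

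Under Sample size, power is stated for the difference "between each active treatment arm and the standard intervention arm of at least 4" per cent. No expected difference between B and C is given.

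**The concern.** A significance test of the total B versus C difference is a poor filter for a mediation question. A non-significant total shows only that the difference was not distinguished from zero. It does not show that the cognitions of those who return the questionnaire are the same in both arms, or that such differences do not matter for uptake.

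The Background supplies the case where this bites. If the voucher recruits returners with less-positive attitudes, uptake gains little, and the cognition data would say why. A small difference is also the one least likely to reach significance.

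The condition has a second effect. If the true difference is small, the trials that meet the condition are those where chance made the estimate large. A mediated share computed only in those trials is divided by a total that is too big.

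At stake is the interpretation of one secondary analysis, not the estimate of whether either invitation works.

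**Working it through.** **Inputs from the protocol article**

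- 4,263 per arm, 12,789 in total, power above 90% (Sample size: "With 4,263 participants in each trial arm, with 12,789 in total, this provides more than 90% power to detect a difference in uptake").
- Planning uptake: "the underlying proportion of people invited who actually receive a Health Check is about 50" per cent (Sample size).
- Local uptake: "32% of individuals invited for a Health Check attended in one borough, and 38%, in the other" (Setting and participants); midpoint 35%.
- Level: 5% with Bonferroni for three comparisons, 0.05/3 = 0.0167, taken as two-sided, so z = 2.394.

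**Assumed, because not stated:** the true C−B difference (1 to 4 points) and uptake in B. The worked case takes B at 35% + 4 points = 39%; the range is 36% to 54%.

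**1. The plan's own figure.** For 50% versus 54%, level 0.0167, power 90%:

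n₀ = [2.394 √(2p̄q̄) + 1.282 √(p₁q₁ + p₂q₂)]² / 0.04² = 4,212.6.

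With continuity correction, n = (n₀/4)[1 + √(1 + 4/(0.04 n₀))]² = 4,262.5, which rounds up to 4,263. The stated figure is reproduced. Without the correction, power at 4,263 is 90.4%.

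**2. Chance that the condition is met.** SE = √[(p_B q_B + p_C q_C)/4263] and power = Φ(d/SE − 2.394).

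For d = 2 points and B = 39%: SE = √[(0.39×0.61 + 0.41×0.59)/4263] = 1.061 points; d/SE = 1.885; Φ(−0.509) = 31%. The observed difference must exceed 2.394 × 1.061 = 2.5 points to count as significant.

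**3. Overestimation once the condition is met.** The mean estimate given significance is d + SE × φ(2.394 − d/SE)/Φ(d/SE − 2.394). For d = 2: 2 + 1.061 × 0.3505/0.3055 = 3.22 points, or 1.6 times the truth.

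| True C−B (points) | Condition met, B = 39% | Range, B = 36–54% | Overestimation |
|---|---|---|---|
| 1 | 7% | 7–8% | 3.0 |
| 2 | 31% | 29–32% | 1.6 |
| 3 | 67% | 65–68% | 1.2 |
| 4 | 91% | 90–92% | 1.05 |

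If significant means unadjusted 5% (z = 1.960), the chances become about 15–16%, 46–48%, 79–82% and 96–97%.

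**4. Effect on a mediated share.** A simulation of 4,000 trials used a true total of 2.0 points, 1.2 indirect and 0.8 direct (60% mediated), with cognitions known for everyone, which is the best case. The condition was met in 31% of trials. In those the total averaged 3.25 points while the indirect effect stayed near 1.2, so the median share mediated fell to 39%.

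**The case against.** The strongest reply has four parts.

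*Scope.* A reader might infer that the plan leaves the voucher's mechanism unexamined whenever B versus C misses significance. It does not. Return by arm and by deprivation, the completer and noncompleter comparisons, and high versus low cognition scores are all analysed regardless, and B versus C uptake is always estimated. This stands; only mediation by cognitions is conditional.

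*Cancelling paths.* A reader might also infer that the Background foresees positive and negative routes that net to zero. It describes a smaller gain, not a harmful path. This stands too.

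*Size.* It is tempting to derive C−B from the plan's figures by letting the 4-point effect act only through returns and doubling the return odds. With an assumed 30% return in B, return in C is 0.60/1.30 = 46.2%, C−B is 4 × (46.2/30 − 1) = 2.15 points, and the condition is met in 36% of trials; across returns of 10% to 50% the figure runs from 75% to 13%. The documents do not support using these as the size of this problem. No return rate is stated, 4 points is a difference to detect rather than a forecast, and in a return-only model cognitions mediate nothing. Under the same model with the earlier questionnaire study's difference (68.3 − 53.5 = 14.8 points), C−B is at least 4.9 points for returns up to 50%, and the analysis is skipped in under 2% of trials.

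*Harm.* Cognitions are measured only in returners, a group the voucher itself changes, so running the analysis more often reports a selection-affected estimate more often. That calls for a caveat, but the condition does not cure it: the same selection is present when B versus C is significant.

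Requiring a total effect before asking what mediates it is also a familiar convention. For an exploratory analysis it protects little.

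**Conclusion.** The point holds in a limited form. The condition is explicit in the text, it is not needed for an exploratory analysis, and it tends to block the cognition analysis in the less-positive-returner scenario that the Background raises. How often it would block, and how much it would distort, depends on a true C−B difference that the plan does not state. At 1 to 3 points the analysis would be skipped in roughly a third to nine-tenths of trials, and the total overestimated 1.2 to 3.0 times when it runs. At 4 points, skipping is about 9% and the overestimation about 5%. These figures assume the Bonferroni level and an unadjusted two-proportion comparison, as in the plan's own calculation. The understated share matters only if a share is reported; the article does not say that one will be. The primary, cost and inequality results are untouched, so this is a minor improvement.

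**What to change.** Delete the opening condition of the sentence on mediation under Secondary analyses. Then:

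- Run the B versus C cognition analysis whatever the P value, and include a comparison of returners' cognition scores by arm.
- Report direct and indirect effects as absolute differences in uptake with confidence intervals, in keeping with the plan's preference for absolute measures.
- Label the analysis exploratory, and state that cognitions are measured only in returners, whose make-up the voucher alters, so the components are not protected by randomisation.

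Nothing further is needed on return rates, which the plan already analyses by arm and deprivation. The cost is one clause and a little analysis time, with no new data. The downside is one more exploratory result that may be imprecise.

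### Cognition scores exist only for people who return the questionnaire, and the voucher is meant to change who returns it, so cognitions among returners cannot show what mediated a difference between Groups B and C

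*Protocol article*

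**What the plan says.** The mediation analysis is in the protocol article under Secondary analyses. Its trigger is a comparison of arms: "If significant differences in uptake appear between the QBE and QBE + incentive arms", then "we will examine whether these are mediated by differences in cognitions".

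The same section shows where the mediator comes from. It asks whether holding more favourable cognitions "about the Health Check, when completing the QBE questionnaire is associated with increased rates of attendance", and the planned contrast is between "positive completers (those with high scores on the cognitions) and negative completers (those with low scores on the cognitions". No other source of cognition scores is described.

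Under Interventions, Groups B and C receive the same questionnaire and the same invitation. They differ in the covering letter, in which Group C "participants are offered a £5 retail voucher as an incentive to return the questionnaire".

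The Background gives the reason for the voucher. A systematic review is summarised as finding that "the odds of returning a postal questionnaire were almost doubled if a financial incentive was offered", and the article infers that "incentivizing questionnaire return may increase the size of any effect of a questionnaire on uptake".

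The section on socioeconomic inequalities gives two possibilities for who the extra returners would be. One is: "The offer of a financial incentive may increase questionnaire return rates only among those with already positive attitudes toward NHS Health Checks". The other is that the offer draws returns from people whose attitudes are less positive, with less effect on uptake.

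**The concern.** The mediator is seen only after a post-randomisation event, the return of the questionnaire, and the contrast between C and B is designed to change that event. Two problems follow.

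1. Returners in B and returners in C are self-selected, possibly in different ways. A difference in their mean cognition mixes any voucher effect on cognition with a difference in who answered.
2. The effect to be explained is the uptake difference between arms, which the article analyses in all randomised patients. Scores from returners alone cannot split that difference into a part that runs through cognitions and a part that does not.

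At stake is an explanatory claim. The report could say that the voucher worked, or failed, through attitudes or intentions when nobody's cognitions had changed.

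**Working it through.** **The plan's own figure.** The article gives no figure for the mediation analysis. The arm size used below does reproduce. For 50% versus 54%, two-sided alpha 0.05/3 (two-sidedness is my assumption) and 90% power, the two-proportion formula with continuity correction gives 4,263 per arm, and 3 × 4,263 = 12,789, both as stated.

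**Return rates.** None is stated, so I assume return in B of r = 20%, 30% or 40%. I take the odds ratio as 2, rounding up the review result quoted in the Background.

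- Return in C: odds = 2r/(1 − r), so r_C = 2r/(1 + r).
- Net excess as a share of C's returners: (r_C − r)/r_C = (1 − r)/2.

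| Return in B | Return in C | Scores missing, B | Scores missing, C | Returners of 4,263, B / C | Net excess share of C's returners |
|---|---|---|---|---|---|
| 20% | 0.40/1.20 = 33% | 80% | 67% | 853 / 1,421 | 0.80/2 = 40% |
| 30% | 0.60/1.30 = 46% | 70% | 54% | 1,279 / 1,968 | 0.70/2 = 35% |
| 40% | 0.80/1.40 = 57% | 60% | 43% | 1,705 / 2,436 | 0.60/2 = 30% |

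**What selection does to the mean.** Suppose the voucher changes nobody's cognitions and deters nobody from returning. Let s be the net excess share and d the mean score of the extra returners minus that of people who would return anyway. Then

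mean(C returners) − mean(B returners) = s × d.

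With s = 0.35 and a purely illustrative d of 1 point on the 7-point scale:

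- extra returners less positive (d = −1): −0.35 points;
- extra returners more positive (d = +1): +0.35 points;
- return unrelated to attitude (d = 0): 0.

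Over s = 0.40 to 0.30, the shift for |d| = 1 is 0.40 to 0.30 points. The usual indirect effect multiplies this shift by the slope of uptake on cognition. If that slope is positive, as the article expects, the spurious indirect effect takes the sign of d.

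**Illustrative simulation.** Each scenario had 2 million people. Return in B was 20% or 30%, the odds ratio about 2, and the voucher had no effect on cognitions. Returning raised uptake by 10 points. Attitude had SD 1, and its effect on the log-odds of return was 0, 0.5 or 1.0 per SD, with this slope unchanged or 0.25 lower under the voucher.

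| | Return depends on attitude | Return unrelated to attitude |
|---|---|---|
| C − B cognition, all randomised | about 0 | about 0 |
| C − B cognition, returners only | −0.07 to −0.24 | about 0 |
| Indirect effect on uptake, returners only (true value 0) | −0.4 to −1.4 points | about 0 |
| C − B uptake, all randomised | +1.2 to +1.7 points | +1.4 to +1.6 points |

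The uptake gain came wholly through return: 0.10 × (33.3% − 20%) = 1.3 points, or 0.10 × (46.2% − 30%) = 1.6 points. The simulated scenarios cover only extra returners with lower scores. The positive sign rests on the formula s × d.

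**The case against.** **The target is one conditional sentence in a condensed article.** The mediation method it cites and any statistical analysis plan are not shown, so non-returners may be dealt with there. That stands for the details. It does not remove the point, because the choice of mediator and its source are fixed here, and no method recovers non-returners' cognitions without added assumptions.

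**Cognitions are a reasonable thing to study.** The inequalities section suggests that the questionnaire makes attitudes more accessible, and it asks whose returns the voucher would bring in. This also stands. It supports describing cognitions by arm, but not a mediation claim.

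A reader might also infer stronger things that the article does not support:

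- *That the voucher will recruit people with less-positive attitudes, so mediation will come out reversed.* The article gives both directions. Sign and size are unknown, and the 1-point gap above is only an illustration.
- *That return is ignored.* Secondary analyses compares uptake in completers and noncompleters in both questionnaire arms and analyses response rate by arm. Return is not, however, put forward as the pathway for the difference between C and B.
- *That this £5 voucher is expected to double the odds of return.* The figure is a review result for financial incentives in general.
- *That 30–40% of C's returners are there only because of the voucher.* The figure is a net excess. It identifies individuals only if the voucher deters no one.
- *That return would be a clean replacement mediator.* Return is also post-randomisation and may share causes with uptake, including attitudes unmeasured in non-returners. Analysing everyone randomised solves the missing scores but not this confounding.

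**Conclusion.** The point holds as a limit on interpretation. Followed as written, the plan would seek to explain a difference between randomised arms from scores held by self-selected returners, with selection that the voucher is meant to alter. The share of patients without a score would be large in both arms: 80–60% of B and 67–43% of C, if return in B is 20–40% and the odds ratio is 2. Bias in the indirect effect requires return to depend on attitude. Its sign then follows whichever kind of person the voucher brings in, and without that dependence it is about zero. The analysis is secondary and runs only after a significant difference between B and C. The primary outcome, the sample size and the intention-to-treat comparison are not touched. This is a cheap improvement.

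**What to change.** Replace the mediation sentence in Secondary analyses. Report cognition scores by arm among returners as a description of who responds, labelled exploratory and subject to selection, with no claim that they mediate the difference between B and C.

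If a pathway analysis is wanted, examine questionnaire return, which is known for everyone randomised to B and C. State the assumptions: either no unmeasured confounding of return and uptake, or, if arm is used as an instrument for return, that the voucher offer affects uptake only through return and deters no one from returning. Add a sensitivity analysis for departures from them.

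The cost is a change of wording and an analysis of data already held. The causal claim about cognitions is given up.
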